**Protocol version:**

V.2, 20 January 2020

Strengths and limitations of this studyThis study uses a pilot randomised control design to explore the safety, acceptability and feasibility of providing the HOLOBalance intervention compared with an established home exercise programme.The HOLOBalance programme provides an individualised training programme prescribed by a treating clinician which addresses all facets of the postural control system.The HOLOBalance study will use quantitative and qualitative data to explore the acceptability of providing holographic balance training programmes to older adults at risk for falls.This study will provide crucial insight into the feasibility of implementing state-of-the-art technologies in the home environment.This pilot study is not powered to determine whether HOLOBalance reduces falls risk or falls rate.

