### Interventions

Participants will be randomised to receive either the active intervention (HOLOBalance) or the control intervention (OTAGO HEP). Participants will be asked to perform their prescribed exercises daily, with each participant performing 40–60 min of rehabilitation per day (including rest breaks). Participants will receive home visits from their treating clinician at week 0, 3 and 6 to assess and progress their programme. All participants will have a telephone conversation with their treating clinician every week for the duration of their participation in the rehabilitation programme to discuss their exercise programme.

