### Outcome measures

#### Primary outcomes

The primary outcomes will relate to the acceptability, safety and feasibility of providing the HOLOBalance intervention. Acceptability measures include; recruitment rate (percentage of eligible participants enrolled), compliance with interventions (percentage of prescribed sessions completed in HOLOBalance and control groups) and drop-out rates (number of drop-out in HOLOBalance and control groups). Exit interviews will be completed with participants that receive the HOLOBalance intervention to explore their experience of using the system, including perceived benefits, frustrations and recommendations. Interviews will be recorded, transcribed verbatim and subject to thematic analysis.

In the HOLOBalance group, adherence will automatically be monitored through the interaction with the system, and calculated as the number of prescribed balance exercises, auditory and cognitive training tasks completed per day, expressed as a percentage. In the control group, participants will be required to complete a daily exercise diary to report on their level of activity, whether they had completed their HEP session and whether they had performed their cognitive tasks. All participants will receive a weekly telephone call from the research physiotherapist to discuss any issues, their current progress and to remind them to complete their exercise diaries (if in the control group) which will be collected at their final outcome measure test session. The order of events for participants enrolled in this study is displayed in table 2.

**Table 2 T2:** Order of events for all participants enrolled in the HOLOBalance study

		Screening session	Baseline test session	Week 0	Daily	Weekly	Monthly	Week 3	Week 6	Follow-up test session	Week 9
Recruitment Procedures	Provide patient information sheet	X									
	Provide informed consent		X								
University-based data collection	Demographics		X								
	The MoCA		X							X	
	The RAPA		X							X	
	The WHODAS 2.0		X							X	
	The CANTAB		X							X	
	The ABC Scale		X							X	
	The FES-I		X							X	
	The EQ-5D		X							X	
	The EMA		X							X	
	The BREQ-3		X							X	
	Mini-BESTest		X							X	
	The FGA		X							X	
	Exit Interviews (HOLOBalance Group Only)										X
Usability Measures	The SUS								X		
	The UEQ			X				X	X		
Home-based interactions	Equipment installation and Removal (HOLOBalance Only)			X						X	
	Home visit from Physiotherapist			X				X	X		

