	Telephone conversation with physiotherapist					X					
	Perform Home Exercise Programme				X						
	Submit falls diaries						X				

ABC, Activities Specific Balance Confidence Scale; BREQ-3, Behavioural Regulation in Exercise Questionnaire; EMA, Environmental Analysis of Mobility Scale; FES-I, Falls Efficacy Scale International; FGA, Functional Gait Assessment; mini-BESTest, Mini Balance Evaluation Systems Test; MoCA, Montreal Cognitive Assessment; RAPA, Rapid Assessment of Physical Activity; SUS, System Usability Scale; UEQ, User Experience Questionnaire; WHODAS 2.0, WHO Disability Assessment Schedule 2.

Safety of the HOLOBalance intervention will be assessed by recording and assessing all adverse/serious adverse events and device effects (and reporting these to appropriate agencies as required). These will be reported by participants to their treating clinician or by self-reporting on the HOLOBalance database. The feasibility of the study will be explored by collecting information on and analysing any deviations from protocol or problems with implementing the study protocol (eg, logistical problems).

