### Data management and statistical analysis

Anonymised data will be entered into a study database. The integrity of this data will be assessed by taking a random sample (10%) from the study database (after the completion of data collection) and comparing with the paper case report form (CRF). If there is less than 98% agreement between the paper CRF record and inputted measures, all data will be checked and rectified. The rectified database will be saved under a new filename (eg, studydatabase_rectified_date) and all changes made to the database will be logged. Essential trial documentation will be kept with the Trial Master File and Investigator Site Files. The sponsor will ensure that study documentation is retained in accordance with their local approvals after the conclusion of the trial.

As this is a proof-of-concept study, there is no formal plan for statistical analysis due to the small sample size and lack of statistical power. However, for a future trial an analysis plan has been developed which will be run in this study to determine its appropriateness. We will use intention to treat analysis with repeated measures general linear model analysis of variance for selected outcome measures and other appropriate tests for between-group and within-group analysis. We will also include correlations analysis and χ^2^ assumption testing.

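### One of the two adverse-event reporting routes appears open only to the HOLOBalance arm, so any between-arm comparison of safety is at risk of unequal ascertainment

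*Protocol article*

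**What the plan says.** The Primary outcomes section of the protocol article makes safety one of three primary themes: "The primary outcomes will relate to the acceptability, safety and feasibility of providing the HOLOBalance intervention". It then says how safety is measured: "Safety of the HOLOBalance intervention will be assessed by recording and assessing all adverse/serious adverse events and device effects". The reporting rule follows: "These will be reported by participants to their treating clinician or by self-reporting on the HOLOBalance database".

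The strengths and limitations box adds a comparator. It describes the randomised design as a means to "explore the safety, acceptability and feasibility of providing the HOLOBalance intervention compared with an established home exercise programme".

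Other passages bear on who can use each route:

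- Table 2 has the row "Equipment installation and Removal (HOLOBalance Only"), so the control arm has no system at home.
- The control arm keeps a paper record instead: "In the control group, participants will be required to complete a daily exercise diary to report on their level of activity". Its other listed contents are completion of the exercise session and of the cognitive tasks. Adverse events are not listed.
- Under Data management and statistical analysis the trial-wide store has a different name: "Anonymised data will be entered into a study database". It is checked against paper case report forms.
- Both arms share clinician contact. Under Interventions, "All participants will have a telephone conversation with their treating clinician every week", and home visits take place at weeks 0, 3 and 6.
- Falls diaries (Secondary outcomes, Balance assessment) are returned monthly and are not limited to one arm.

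**The concern.** A comparison of event counts between arms is fair only if an event has the same chance of being recorded in each arm. Here one arm seems to have a self-report channel in addition to the clinician, and no equivalent is described for the other. An extra channel can add recorded events but cannot remove them, so any distortion goes one way, towards more recorded events on HOLOBalance.

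The Blinding section says that neither participants nor treating clinicians can be blinded. Equal ascertainment is then the main protection that an adverse-event contrast has. Without it, a difference between arms can be misread in two ways: an artefact of reporting may be taken for harm, or a true excess may be dismissed as an artefact. An analysis plan cannot repair this later, because control-arm events that were never captured cannot be recovered.

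**Working it through.** **Step 1. Who has the second route?** The reporting rule does not restrict access to the HOLOBalance database. Three facts point to the HOLOBalance arm alone: the equipment is installed in that arm only, the control diary does not list adverse events, and the trial-wide store is called the study database and is checked against paper forms. Arm-specific access is the natural reading, but it remains an inference.

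**Step 2. Is safety compared between arms?** The Primary outcomes section defines compliance and drop-out for both groups but frames safety around HOLOBalance. The comparison with the established programme is stated only in the strengths and limitations box. No test, margin or event rate is given. The stated sample size, 60 + 60 = 120, is not derived from any safety figure, so there is no safety calculation in the plan to reproduce.

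**Step 3. How large could the distortion be?** The document gives no capture rates, so these are assumptions:

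- *c* = share of events captured by the shared clinician route (calls and visits);
- *e* = share captured by the database, independently of the clinician route;
- true event rates are equal in the two arms.

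The recorded share is *c* in control and 1 − (1 − *c*)(1 − *e*) in HOLOBalance. Hence

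recorded ratio = [1 − (1 − *c*)(1 − *e*)] / *c* = 1 + *e*(1 − *c*)/*c*.

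| Clinician capture *c* | *e* = 0.2 | *e* = 0.5 |
|---|---|---|
| 0.5 | 1 + 0.2 × 1.000 = 1.20 | 1 + 0.5 × 1.000 = 1.50 |
| 0.8 | 1 + 0.2 × 0.250 = 1.05 | 1 + 0.5 × 0.250 = 1.13 |
| 0.9 | 1 + 0.2 × 0.111 = 1.02 | 1 + 0.5 × 0.111 = 1.06 |
| 1.0 | 1.00 | 1.00 |

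If people who log an event also tend to mention it on the call, the routes overlap and the ratios shrink.

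**Step 4. The same on the scale of participants.** Assume a true risk of 20% in each arm, with 60 per arm.

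- *c* = 0.8, *e* = 0.5: control 0.20 × 0.8 = 16% (9.6 participants); HOLOBalance 0.20 × (0.8 + 0.2 × 0.5) = 18% (10.8 participants). Spurious difference: 2 points.
- *c* = 0.6, *e* = 0.75: control 0.20 × 0.6 = 12% (7.2 participants); HOLOBalance 0.20 × (0.6 + 0.4 × 0.75) = 18% (10.8 participants). Spurious difference: 6 points.

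Over true risks of 10% to 40%, *c* from 0.6 to 1.0 and *e* from 0 to 0.75, the spurious difference runs from 0 to 12 points.

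For scale, the 95% half-width of a difference is 1.96 × √(2*p*(1 − *p*)/60). That is 10.7 points at *p* = 10% and 17.5 points at *p* = 40%. The distortion is often smaller than the sampling error, but it is systematic and always has the same sign.

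**Step 5. With equal routes.** Setting *e* = 0 gives a ratio of 1.00 for every *c*.

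**The case against.** The strongest reply is that safety is essentially a one-arm description. The abstract's aim concerns the safety of providing HOLOBalance, device effects cannot occur in controls, and the Trial design section names acceptability as what is compared. For a one-arm description an extra route improves capture. This stands as far as it goes, and no formal safety comparison is defined. But the strengths and limitations box does set safety against the established programme, and side-by-side counts are distorted in the same way as tested ones.

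Second, the database name may not imply exclusive access, since the whole trial carries the HOLOBalance name. That stands as a limit on certainty. The separately named study database makes the arm-specific reading the more likely one.

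Third, the arms share a good deal of ascertainment: weekly calls made to everyone, three home visits, and falls diaries. This also stands. It is why high clinician capture, and so a small distortion, is plausible, and why falls can be compared from a common source. It narrows the gap without guaranteeing that it closes for other events.

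Fourth, call scripts and adverse-event forms commonly sit in the full protocol, which is not shown. Their absence from the article is therefore no fault. The point rests only on the unequal routes that the article states.

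A reader might go further and infer that the primary safety comparison is biased and that the control arm offers no usable safety reference. The documents do not support that. Exclusive access is inferred, the size of any bias is unknown and may be nil, and events from the shared routes remain comparable if their route is recorded.

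**Conclusion.** The point holds as a risk of bias. On the natural reading of the reporting rule, any between-arm comparison of the primary safety outcome, including a descriptive one, may over-record non-fall events on HOLOBalance. Falls are less exposed because of the common diaries.

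The size cannot be fixed from the document. With independent database capture of 20% to 50% and equal true rates, the recorded ratio is about 1.0 to 1.1 if the shared clinician route captures 80% to 90% of events, and 1.2 to 1.5 if it captures 50%. It is exactly 1 if the shared route is complete or if both arms can use the database. The conclusion rests on the inference that only the HOLOBalance arm can self-report on that database. The description of HOLOBalance safety on its own is not weakened. The change is worth making because it is cheap and must be in place while data are being collected.

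**What to change.** - State who can self-report on the HOLOBalance database.
- Ask the same scripted adverse-event question in the weekly calls already planned for both arms.
- Record the route of each event on the adverse-event form. Count an event given by both routes as a common-route event.
- Limit any between-arm safety comparison to events from the common routes (calls, visits and falls diaries), expressed per participant-week.
- Report database-only self-reports and device effects separately, labelled as HOLOBalance-only data.

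The cost is slightly longer calls and one extra field on the form. No additional contact or equipment is needed.

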### Secondary outcomes

#### Balance assessment

The mini balance evaluation systems test^55^ (mini BESTest) is a 14-item test that assesses dynamic balance components including anticipatory postural adjustments, reactive postural control, sensory orientation and dynamic gait. The data are based on a total score of 28 points. The test takes approximately 10 min to complete. This will be collected at baseline (week 0) and follow-up (week 9)

The Functional Gait Assessment^4^ (FGA) is a 10-item test that assesses performance on complex gait tasks (eg, walking with head turns or stopping and turning). The test takes approximately 5 min to complete. Scores of 21 or less indicate risk for falls.^4^ This will be collected at baseline (week 0) and follow-up (week 9).

Falls diaries will be used to record whether participants have fallen each day, with falls defined as a person coming to rest inadvertently on the ground or floor or other lower level. Participants will return falls diaries monthly for the duration of the intervention and for 6 months after completion.

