## Methods and analysis

### Trial design

This study is an assessor-blinded, randomised proof-of-concept study to explore the acceptability and feasibility of providing a home-based balance telerehabilitation programme (HOLOBalance) to community-dwelling older adults at risk for falls. All participants will be enrolled in a 8-week home exercise programme (HEP) designed to improve balance function, and which adheres to the current guidance for strength and balance training.^30^ All participants will receive an exercise programme provided under the supervision of a physiotherapist with regular reviews by telephone (weekly) and home visits (week 0, 3 and 6). Exercises will be prescribed according to participant feedback and task performance as assessed by the treating physiotherapist.

This study will compare acceptability of the HOLOBalance telehealth programme (eg, compliance, drop-out rate) to an established HEP that is routinely used in community rehabilitation (the OTAGO HEP^23^) and will explore trends for effectiveness across a number of validated outcome measures to explore whether a future trial is warranted, and if so to provide data for a sample size estimate. For this proof-of-concept study, data will be collected at baseline (week 0) and at completion of the intervention (week 9). The flow of participants through the trial will be recorded in compliance with the Consolidated Standards of Reporting Trials statement (figure 1), and this protocol has been developed using the Standard Protocol Items: Recommendations for Interventional Trials reporting guidelines for clinical trials.^48^

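### As stated, the primary safety outcome does not draw on the daily falls diary, the one falls record described as common to both arms

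*Protocol article*

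**What the plan says.** Under Primary outcomes, the protocol article states that "The primary outcomes will relate to the acceptability, safety and feasibility of providing the HOLOBalance intervention". The safety part is then defined: "Safety of the HOLOBalance intervention will be assessed by recording and assessing all adverse/serious adverse events and device effects". The source of these events follows: "These will be reported by participants to their treating clinician or by self-reporting on the HOLOBalance database". Falls are not named in this definition, and the falls diary is not given as a source.

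The diary appears under Secondary outcomes, Balance assessment. There, "Falls diaries will be used to record whether participants have fallen each day", with a definition of a fall. Its duration is also given: "Participants will return falls diaries monthly for the duration of the intervention and for 6 months after completion". Table 2, whose title covers all participants, marks diary submission in its monthly column.

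Both arms have a weekly call with the physiotherapist during the 8-week programme and home visits at weeks 0, 3 and 6 (Interventions). The stated content of the call is issues, progress and, in the control arm, a reminder about the exercise diary (Primary outcomes).

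**The concern.** Falls are the harm most to be expected here. Participants can qualify through a low gait score, fear of falling or a fall in the past year. They then exercise daily at home, and Table 1 includes standing on foam and closing the eyes for the HOLOBalance arm, which also wears a head-mounted display. A fall can thus be both an efficacy measure and a harm, and the article assigns the diary to the first role only.

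The primary safety count as written depends on a participant telling a clinician, who is not blinded, or making an entry on a database. The diary asks every participant the same question about every day. If ascertainment through the first route differs between arms, the safety comparison inherits that difference, while a more even record sits elsewhere in the report. No on-treatment window for diary falls is fixed either, so a reader of the results could be given falls over the whole diary period with no separate view of the weeks of exposure.

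**Working it through.** **1. The two records side by side**

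| | Primary safety outcome | Falls diary |
|---|---|---|
| Place in the article | Primary outcomes | Secondary outcomes, Balance assessment |
| What is recorded | Adverse events, serious adverse events, device effects | Whether the person fell, each day |
| How it is obtained | Report to the treating clinician, or self-report on the HOLOBalance database | Diary returned monthly |
| Same in both arms? | Clinician route yes; database route unclear | Yes, by Table 2 |
| Period | Not stated | 8-week programme plus 6 months |

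The database row is an inference. The name suggests the intervention system, but the study bears the same name, so the article does not settle whether control participants have access.

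**2. Share of the diary window that is off-treatment**

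Inputs: an 8-week programme (Trial design) and 6 months of diaries afterwards (Balance assessment), taken as 26 weeks.

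Off-treatment share = 26 / (8 + 26) = 26/34 = 76.5%.

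Sensitivity: with 24 weeks for 6 months, 24/32 = 75.0%. With 9 on-treatment weeks, 26/35 = 74.3% or 24/33 = 72.7%. About three-quarters holds throughout.

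**3. Expected control fallers during the programme**

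Inputs: 60 per group (Sample size); one in three people over 65 falls each year (Introduction). The enrolled group is selected for risk, so annual proportions of 50% and 60% are added as assumptions. With a constant hazard, the 8-week risk is 1 − (1 − p)^(8/52). A doubled hazard gives 1 − (1 − p)^(16/52).

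Power is for comparing the two proportions with 60 per arm at two-sided 5%, using the normal approximation with pooled variance under the null.

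| Annual proportion p | 8-week risk, control | Fallers per 60 | 8-week risk, hazard doubled | Fallers per 60 | Power | n per arm for 80% power |
|---|---|---|---|---|---|---|
| 1/3 (article) | 6.0% | 3.6 | 11.7% | 7.0 | 19% | 393 |
| 50% (assumed) | 10.1% | 6.1 | 19.2% | 11.5 | 29% | 237 |
| 60% (assumed) | 13.1% | 7.9 | 24.6% | 14.7 | 36% | 184 |

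The article gives no power calculation for its 120 participants, so there is no figure of its own to reproduce. With roughly 4 to 8 control fallers, one faller missing from the safety record is between 1/8 (12.5%) and 1/4 (25%) of the control count. That shows how sensitive the count is; it is not an estimate of how many would be missed.

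**4. Does a yes/no entry per day lose falls?**

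Under a Poisson model at these rates, about 0.06% to 0.13% of fall-days would contain a second fall. Clustering would raise this, but the daily format is adequate for counting.

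**The case against.** The strongest reply is that falls are already inside safety. The article covers "recording and assessing all adverse/serious adverse events and device effects", and weekly calls and home visits in both arms give regular chances to report, so an injurious fall in particular is unlikely to go unheard. Not naming the diary is not the same as excluding it. The article is also a condensed protocol: diary fields, adverse-event coding and the handling of late diaries normally sit in the full document, and their absence here is no fault. All of this stands. It narrows the point to the stated sources of the primary outcome. The article says which routes feed safety, and the diary is not among them. It gives no falls question for the weekly call, and whether a fall without injury counts as an adverse event is left open.

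A second reply is that the pilot disclaims power for falls. That disclaimer concerns showing a reduction in falls risk or rate. It does not remove the need to describe harms completely and equally by arm.

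Several stronger readings are tempting, and the document does not support them:

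- **That safety cannot show whether HOLOBalance causes falls because of the diary design.** Entries are daily, so falls in the treatment weeks can be separated by date. The limit on a causal conclusion is sample size.
- **That an on-treatment excess will be diluted over 34 weeks.** This needs a pooled analysis that the article never states.
- **That the exercise is unsupervised.** It is done independently, but under a physiotherapist's supervision with calls and visits.
- **That Trial design contradicts the 6-month diaries.** That section gives the baseline and week 9 assessments without saying that nothing else is collected, and the usability measures are taken at other times.

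**Conclusion.** The point holds as a matter of outcome definition. A primary safety outcome in people at risk of falls is stated without its most complete and symmetric source on falls, although those data are collected in both arms anyway. About three-quarters of the diary window (72.7% to 76.5%) is off-treatment, so an on-treatment window needs to be named for the diary to serve safety.

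The gain is in complete and equal descriptive capture. It is not a test of causation: with about 4 to 8 control fallers expected per 60, power for a doubled hazard is only 19% to 36%. These figures rest on a constant hazard and on annual proportions of one-third (from the article) to 60% (assumed). The possible difference between arms in database access is inferred from its name only. The full protocol, which is not shown, may already link diary falls to the adverse-event record; if so, the article needs only a sentence saying so.

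**What to change.** 1. Name diary-recorded falls from first session to week 9, in both arms, as a component of the primary safety outcome.
2. Report them by arm as number of falls and number of fallers with confidence intervals, without a formal test, and separately from falls in the 6 months after the programme. The later falls can stay a secondary outcome.
3. At the existing weekly call, ask participants in both arms the same questions: whether any fall occurred, whether it caused injury, and whether it happened during an exercise session. The last bears on device effects, which the safety outcome already includes.

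The cost is a wording change to the outcome section and the call script, a slightly longer call and a few more events to log. No extra visits or staff are needed.
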